### Study outcomes

The co-primary outcomes will be changes on markers of cardiovascular health and low-grade inflammation following 24 months of supplementation. Secondary outcomes include changes on selected indicators of ageing, upper respiratory tract symptoms and quality of life. Finally, tertiary outcomes include plasma concentration changes of vitamins, carotenoids and fatty acids.

A detailed summary of all parameters to be assessed is given in Table 2.

**Table 2 Tab2:** Detailed summary of primary, secondary and tertiary outcome parameters

Primary outcomes	Low-grade inflammation
Cardiovascular health	
Total cholesterol, LDL, HDL, ApoA1, TG, oxLDL, homocysteine, omega-3 Index, platelet aggregation, TEM, coagulation (PT, PTT), glucose, insulin, HOMA-IR, HbA1c, MDA, CP, redox state of albumin	TNF-α, sTNFR1 and sTNFR2, CCL5, IL-1β, hsCRP, CCL2, OPG, IL-5, IL-8

Secondary outcomes	Upper respiratory tract symptoms	Quality of life
Selected indicators of ageing		
uc-osteocalcin, dp-ucMGP, mtDNA-CN, BDNF, NGF, CFD index	WURSS-21	SF-36

Tertiary outcomes	Fatty acids
Vitamins and carotenoids	
Retinol, vitamins C, D, E (α-tocopherol and γ- tocopherol), K1, K2 (MK-7), α-carotene, β-carotene, lutein, zeaxanthin, lycopene, β-cryptoxanthin	DHA, DPA, EPA, AA, ALA, linoleic acid, oleic acid, palmitoleic acid, stearic acid

*AA* arachidonic acid, *ALA* alpha-linolenic acid, *ApoA1* apolipoprotein A1, *BDNF* brain-derived neurotropic factor, *CCL2* chemokine (C–C motif) ligand 2, *CCL5* chemokine (C–C motif) ligand 5, *CFD index* cognitive functions dementia index, *CP* carbonyl proteins, *DHA* docosahexaenoic acid, *DPA* docosapentaenoic acid, *dp-ucMGP* dephosphorylated-uncarboxylated Matrix GLA protein, *EPA* eicosapentaenoic acid, *HbA1c* haemoglobin A1c, *HDL* high-density lipoprotein, *HOMA-IR* homeostatic model assessment of insulin resistance, *hsCRP* high-sensitivity C-reactive protein, *IL-1β* interleukin 1-beta, *IL-5* Interleukin-5, *IL-8* interleukin-8, *LDL* low-density lipoprotein, *MDA* malondialdehyde, *mtDNA-CN* mitochondrial DNA copy number, *NGF* nerve growth factor, *OPG* osteoprotegerin, *oxLDL* oxidised low-density lipoprotein, *PT* prothrombin time, *PTT* partial thromboplastin time, *SF-36* 36-Item Short Form Health Survey, *sTNFR1* soluble tumour necrosis factor receptor 1, *sTNFR2* soluble tumour necrosis factor receptor 2, *TEM* thrombelastometry, *TG* triglycerides, *TNF-α* tumour necrosis factor alpha, *uc-osteocalcin* undercarboxylated osteocalcin, *WURSS-21* Wisconsin upper respiratory symptom survey

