#### Blood markers

A total of 47 ml from each participant will be collected by venepuncture by the study physician at each visit for the analysis of blood biomarkers of cardiovascular health, low-grade inflammation, selected indicators of ageing, vitamins, carotenoids and fatty acids. Aggregation and thrombelastometry parameters will be immediately measured in fresh whole blood. 1mL of whole blood will be stored at −80°C for future analysis of mtDNA. Blood samples for the clinical chemistry analyses will be transported immediately after collection to another collaborating laboratory for analysis. Remaining blood will be centrifuged at 3000 rpm for 10 min to get the plasma. The supernatant will be frozen at −80°C and kept at the study site for further analysis.

Blood lipids including total cholesterol, LDL, HDL, triglycerides and ApoA1, as well as homocysteine, hsCRP and vitamin D will be measured by the standard equipment Architect ci8200 (Abbott Diagnostics, IL, USA). Glucose and HbA1c will be measured photometrically using the Alinity system (Abbott, IL, USA) and insulin by the fully automated chemiluminescence analyser LIAISON® XL (DiaSorin, Italy). HOMA-IR will be calculated from glucose and insulin. oxLDL will be analysed by solid phase two-site enzyme immunoassay (Mercodia Inc, Sweden).

Whole blood aggregation parameters, including amplitude, slope and lag time, will be assessed by a Chrono-Log Whole Blood Aggregometer, model 590 from Probe & Go (Endingen, Germany), which is based on the impedance method.

Thrombelastometry (TEM) parameters including coagulation time (CT), clot formation time (CFT), maximum clot firmness (MCF) and alpha angle will be assessed by the TEM coagulation analyser ROTEM®05 (Matel Medizintechnik, Austria). Prothrombin time (PT) and partial thromboplastin time (PTT) will be determined using the apparatus ACL Top LTS 300 (Werfen GmbH, Germany).

Malondialdehyde (MDA) will be determined by high-performance liquid chromatography (HPLC) and carbonyl proteins (CP) by a carbonyl protein enzyme-linked immunosorbent assay (ELISA) kit (Immundiagnostik AG, Germany). Redox state of albumin will be determined by separating albumin into three fractions; human mercaptalbumin (HMA), human non-mercaptalbumin1 (HNA1) and human non-mercaptalbumin2 (HNA2). HMA, HNA1 and HNA2 will be determined by means of HPLC.

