#### Sample size

The sample size calculation was performed according to omega-3 index changes as a key biomarker of cardiovascular health and TNF-α changes as a key biomarker of low-grade inflammation, following supplementation. Assuming a two-tailed t-test using 5% significance level (two-sided), a sample size of 18 and 19 subjects per group was determined to have 80% power to detect a 30% increase on omega-3 index [32] and a minimum decrease of 0.4 ng/L on TNF-α [43], respectively. Allowing for a dropout rate of 30% over 24 months, we aim to recruit 112 participants in total (*n* = 28 control group; *n* = 28 FVB group; *n* = 28 Omega group; *n* = 28 FVBO group).

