### Statistical analysis

Statistical analysis will be performed using the Statistical Package for the Social Sciences (SPSS) software (version 24.0, IBM Corporation, Chicago, IL) by an independent statistician, blinded to participants’ group allocation. Metric data will be presented as mean ± SD. Statistical significance is set at *P* < 0.05. Normally distributed data fulfilling variance homogeneity will be analysed by one- and two-factorial (either ‘time’ or ‘time x treatment’) repeated measures analysis of variance (ANOVA) and covariance within each group and between all groups. Normal distribution will be determined by the Shapiro–Wilk test and homogeneity of variance by the Levene test. For post hoc analyses we will use the Bonferroni(–Holm) correction and/or Tukey’s post hoc test.

If it is not possible to use metric data, nonparametric tests will be used like the Friedman test (within group) and the Kruskal–Wallis test (between groups). If differences between groups reach significance, the Bonferroni–Holm method will be used to determine the localisation of the differences.

In addition, we will conduct comprehensive correlation analyses to compute relations within each outcome category and between the different outcome categories.

Statistical analyses will include data from all participants with an adherence to the study protocol (intervention compliance) of > 80%.

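### Twenty-nine markers are all primary and tested at 5% with no stated control across markers: about a 77% chance of a false-positive primary result if they are independent, less if correlated

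*Protocol article*

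**What the plan says.** Under Study outcomes, the protocol article says: "The co-primary outcomes will be changes on markers of cardiovascular health and low-grade inflammation following 24 months of supplementation". It refers to Table 2 for the detail.

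The cardiovascular column of Table 2 reads "Total cholesterol, LDL, HDL, ApoA1, TG, oxLDL, homocysteine, omega-3 Index, platelet aggregation, TEM, coagulation (PT, PTT" and continues with "glucose, insulin, HOMA-IR, HbA1c, MDA, CP, redox state of albumin". The inflammation column reads "TNF-α, sTNFR1 and sTNFR2, CCL5, IL-1β, hsCRP, CCL2, OPG, IL-5, IL-8". All of these stand under the primary heading. None is singled out.

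The Sample size section rests on two of these markers: "The sample size calculation was performed according to omega-3 index changes as a key biomarker of cardiovascular health", with TNF-α taken in the same way for inflammation. Each calculation uses a two-sided 5% level.

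The Statistical analysis section says "Statistical significance is set at" P < 0.05. Bonferroni(–Holm) or Tukey is planned for post hoc analyses. On the nonparametric route, Bonferroni–Holm is used to find which groups differ.

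**The concern.** Every planned correction works inside one marker, sorting out which of the four arms differ. Nothing in the article limits error across the 29 markers, and nothing says whether one, several or all must be significant. If one is enough, the error rate for the primary outcome is far above 5%, and a positive result could be reported from whichever marker happened to move.

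The design also does not match itself. It has two sized endpoints and 29 declared primaries, so 27 of them have no stated power basis. This bears directly on the trial's main question, whether supplementation affects cardiovascular and inflammatory markers. It cannot be credibly repaired once results by arm have been seen.

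**Working it through.** **1. The plan's own figure.** Sample size gives 18 (omega-3 index) and 19 (TNF-α) per group and 30% dropout. Taking the larger: 19 / (1 − 0.30) = 27.1, rounded up to 28 per arm; 28 × 4 = 112. This matches the stated total. The 18 and 19 cannot be rebuilt because no SD is given. Solving the two-sample t-test for 80% power at two-sided 5% gives implied standardised effects of d = 0.96 (n = 18) and d = 0.93 (n = 19).

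**2. Count of primary markers (Table 2).**
- Cardiovascular, first part, total cholesterol to PTT, with PT and PTT counted separately: 12
- Cardiovascular, second part, glucose to redox state of albumin: 7
- Inflammation, with the two TNF receptors counted separately: 10
- Total: 12 + 7 + 10 = 29

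**3. Error rate, independent markers.** One between-group test per marker at 0.05, all null hypotheses true:
- P(at least one) = 1 − 0.95^29 = 0.774
- Expected false positives = 29 × 0.05 = 1.45

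**4. Error rate, correlated markers.** The article gives no correlations, so these are assumptions. For equicorrelated normal test statistics with correlation ρ:

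P = 1 − ∫ φ(s) [Φ((1.96 − √ρ·s)/√(1−ρ)) − Φ((−1.96 − √ρ·s)/√(1−ρ))]^29 ds

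| Assumed ρ | P(at least one) |
|---|---|
| 0 | 77% |
| 0.3 | 65% |
| 0.5 | 50% |
| 0.7 | 33% |

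**5. The two sized markers alone,** each at an undivided 5% and independent: 1 − 0.95² = 9.75%.

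**6. Power if the level is lowered.** Two-sample t-test, d = 0.93, 19 completers per group:

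| Two-sided level | Where it arises | Power |
|---|---|---|
| 0.05 | as planned | 80% |
| 0.025 | first Holm step over two endpoints | 70% |
| 0.05 / 5 = 0.01 | first Holm step over five contrasts | 57% |

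With d = 0.96 and 18 completers the figures are the same to the nearest per cent.

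**The case against.** **The markers are not independent.** This stands. HOMA-IR is computed from glucose and insulin, both of which are also listed. Total cholesterol with LDL, and TNF-α with its receptors, are plainly related. The 77% is therefore the figure for independence, and the lower figures have to be given with it.

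**The article already points to a lead marker in each domain.** Sample size singles out omega-3 index and TNF-α. This helps, but the choice is not carried into the outcome definition, and each marker is sized at a full 5%.

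**The study is explorative.** The Discussion does say so, as a defence of the open-label design without placebo. It does not relabel the primary outcomes. It does mean that estimates for individual markers remain usable as exploratory evidence.

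**A rule may exist elsewhere.** Only a condensed article is at hand, and a cross-marker rule may sit in the full protocol or analysis plan. The point is therefore limited to what the article fixes: 29 primaries, one significance level and corrections within a marker.

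**Stronger readings that the text does not support.** A reader might count the sub-parameters in the Blood markers section (for example "Whole blood aggregation parameters, including amplitude, slope and lag time"), reach 36 variables and quote 1 − 0.95^36 = 84%. Table 2 lists each of these panels as one entry, and that formula treats readings from the same sample and assay, or fractions of the same albumin, as independent. A reader might also infer that, if all markers must succeed, success is impossible because Table 1 shows no EPA + DHA for the fruit and vegetable capsules. That does not follow: the planned test compares all groups, and the Omega and combined arms can make the omega-3 index test significant by themselves.

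**Conclusion.** The point holds. As written, the plan leaves the false-positive rate of the primary outcome well above 5%: 77% with 29 independent markers, and about 65% to 33% at assumed equal correlations from 0.3 to 0.7. These figures assume one between-group test per marker, no true effect on any marker, and that one significant marker would count as success. Within-group tests are also planned and are not counted here.

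It would be too strong to call a false-positive result close to certain. Even under independence, about 59 tests at 5% would be needed to reach 95% (ln 0.05 / ln 0.95 = 58.4). If every marker had to be significant there would be no inflation, but the article states no such rule.

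**What to change.** In Study outcomes, Table 2 and Statistical analysis, name the changes in omega-3 index and TNF-α at 24 months as the only primary endpoints. Then choose one of two testing schemes.

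1. **Overall tests first.** Apply Holm across the two overall between-group (time × treatment) tests. Go on to arm-versus-control contrasts only for an endpoint whose overall test is significant at its Holm level, using the planned Bonferroni–Holm correction within that endpoint at no more than that level. Holm's second step is at 5%, so if both overall tests succeed the contrast levels could add up to 2.5% + 5% = 7.5%. If claims about individual arms must be held at 5% in all, keep the contrasts at 2.5% per endpoint.
2. **Contrasts directly.** Apply Holm over five named contrasts: omega-3 index for Omega and for the combined arm versus control, and TNF-α for each of the three supplement arms versus control.

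Holm across the two endpoints alone, with the five contrasts then tested freely, would not be enough.

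Move the other 27 markers to secondary, with false-discovery-rate control or with P values labelled exploratory. No measurement is lost. Make the change before any comparison of outcomes by arm.

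**Cost.** Rewording, a registry update and a restated power. For one pairwise comparison at the implied effect with 19 completers per group, power is about 70% at 0.025 and about 57% at 0.01, instead of 80%. No extra enrolment is proposed. For reference, restoring 80% at 0.025 would need 24 completers per group: 24 / 0.7 = 34.3, so 35 per arm and 140 in total.

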### Study visits and procedures

#### Screening visit

Subjects expressing interest to participate in the study will be invited to a screening visit. On the screening visit, a research team member will go through the participant information sheet and explain all study procedures to potential participants. Participants will have the opportunity to ask any questions they might have. If they are still interested to participate, they will be asked to sign an informed consent form, prior to any measurements being taken.

During the screening visit, participants’ medical history will be assessed and measurements of height, weight, BMI and blood pressure (BP) will be taken. Participants meeting the inclusion criteria will be enrolled in the study and an appointment for the baseline visit will be arranged. A minimum of 6-week washout period, to eliminate any interfering nutritional supplements and dietetic products, will be allowed between the screening and baseline visit. Also, in order to avoid a potential effect of physical activity and changed nutritional habits on the measured blood markers, participants will be asked to abstain from any form of strenuous physical activity and complete an estimated food diary, 4 days prior to the baseline visit. Detailed information on how to complete the food diary will be provided during the screening visit.

#### Baseline visit

During the baseline visit, the study physician will assess participants’ history once again to ensure that they still fit the inclusion criteria of the study.

Height, weight, BMI and blood pressure will be measured. Participants will be required to fast overnight and fasting blood samples will be collected by venepuncture, to measure biomarkers of cardiovascular health, low-grade inflammation, indicators of ageing, circulating micronutrients and fatty acids.

Following blood drawing, participants will be offered a snack and then asked to complete the cognitive function test (CFD index). Subsequently, they will complete the Short Form survey (SF-36) and the Perceived Stress Scale (PSS-10) questionnaires, which assess quality of life and stress profile respectively. In addition, participants’ physical activity will be assessed via completion of the International Physical Activity Questionnaire—Short Form (IPAQ-SF).

As part of safety routine, we will perform blood analysis including clinical chemistry [i.e. key biomarkers of liver (aspartate transaminase, alkaline phosphatase, gamma-glutamyl transferase) and kidney function (urea, uric acid, creatinine, glomerular filtration rate)], blood proteins, haemogram and coagulation markers. We will also collect the food diary, which was provided to participants during the screening visit, to assess their nutrition and ensure they do not exceed the fruit and vegetable intake, outlined in the inclusion/ exclusion criteria.

At the end of the baseline visit, participants will be randomly allocated to one of the four groups. Participants in the control group will continue with their habitual diet and lifestyle. Those allocated to the three whole food supplement groups, will have to continue their habitual diet and lifestyle, and will also be provided with the corresponding supplements they will have to ingest. Participants will be asked to avoid disposing of any unused capsules and return any leftovers in the next follow-up visit. In addition, all participants will receive a copy of the Wisconsin Upper Respiratory tract Symptoms Survey (WURSS-21) and the Gastro-Intestinal Symptoms Survey-16 (GISS-16) and will be asked to fill these in every time they experience upper respiratory tract or gastrointestinal symptoms, during the duration of the intervention. They will also be reminded that over the following two years they will have to maintain their habitual diet which must correspond to the nutritional inclusion and exclusion criteria.

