#### Follow-up visits

Follow-up visits at 12 and 24 months will be identical to the baseline visit. Follow-up visits at 6 and 18 months will be the same with the baseline visit, with the only exception that the cognitive function test and mtDNA-CN will not be performed. This is due to the fact that we estimate that more than 6-month time would be required to detect any potential changes in these parameters [34].

Participants will be provided with a copy of the food diary they had completed prior to the baseline visit and will be asked to replicate their diet, 4 days before each follow-up visit, to avoid any potential effect of changed nutritional habits on the measured blood markers. They will also be reminded to avoid any strenuous physical activity during this time. At every follow-up visit, we will collect any WURSS-21 and GISS-16 questionnaires completed during the previous 6 months, from participants that experienced respiratory tract symptoms or gastrointestinal discomfort. We will also collect any leftover capsules from the previous 6 months, to monitor intervention compliance. Participants will be contacted via telephone in between visits with a cadence of 3 months, by a member of the research team, to keep them motivated and ensure maximum retention to the trial.

Figure 1 summarises participants’ recruitment and follow-up plan, according to the Consolidated Standards of Reporting Trials (CONSORT) 2010 statement. Figure 2, provides an overview of the schedule of interventions and all study procedures performed at each study visit, according to the Standard Protocol Items: Recommendations for Interventional Trials (SPIRIT) guidelines [35].

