#### Upper respiratory tract symptoms

For an exploratory assessment of the incidence, duration and severity of upper respiratory tract symptoms, the Wisconsin Upper Respiratory tract Symptoms Survey (WURSS-21) will be used. The WURSS-21 questionnaire contains 21 questions and is an evaluative illness-specific quality of life instrument, designed to assess the negative impact of acute upper respiratory tract infection, presumed viral (the common cold) [41, 42].

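### WURSS-21 is listed as a secondary outcome of change, but no baseline is described and forms are filled in only during symptoms, so its definition and analysis need to fit event data

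*Protocol article*

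**What the plan says.** All references are to the protocol article.

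- **Study outcomes:** "Secondary outcomes include changes on selected indicators of ageing, upper respiratory tract symptoms and quality of life". Table 2 lists WURSS-21 in the secondary block.
- **Baseline visit, questionnaires:** after the cognitive test, "Subsequently, they will complete the Short Form survey (SF-36) and the Perceived Stress Scale (PSS-10) questionnaires", followed by the IPAQ-SF. WURSS-21 is not in this list.
- **Baseline visit, after the sentence on allocation:** "all participants will receive a copy of the Wisconsin Upper Respiratory tract Symptoms Survey (WURSS-21") and the GISS-16, and "will be asked to fill these in every time they experience upper respiratory tract or gastrointestinal symptoms" while the intervention runs.
- **Follow-up visits:** "At every follow-up visit, we will collect any WURSS-21 and GISS-16 questionnaires completed during the previous 6 months", from participants who had symptoms. The same section plans telephone contact every 3 months.
- **Upper respiratory tract symptoms:** the instrument is used "For an exploratory assessment of the incidence, duration and severity of upper respiratory tract symptoms".
- **Statistical analysis:** one plan covers all outcomes. Metric data that meet the assumptions go to "repeated measures analysis of variance (ANOVA) and covariance within each group and between all groups". Otherwise nonparametric tests are used, with Friedman and Kruskal–Wallis as examples. The analysis includes participants with more than 80% compliance.

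**The concern.** Three stated parts of the plan do not fit together.

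1. **Definition against data.** A change needs a value before treatment. The described procedure yields forms only after allocation, and only during illness.
2. **Definition against instrument section.** Study outcomes and Table 2 make this a secondary outcome of change. The instrument section makes it an exploratory assessment of incidence, duration and severity. Incidence is an event rate, not a change, and the two labels differ.
3. **Data against analysis.** Repeated-measures ANOVA and Friedman need one value per person at each time point. Symptom-triggered forms give several values for some people and none for others.

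A further problem lies in the collection itself. Participants decide when to fill in a form, and they know their arm. A participant without a form may have had no episode or may not have recorded one. An analysis plan written later cannot recover that difference.

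At stake is whether the respiratory result can be interpreted. Comparing severity only among people who reported an episode conditions on something that happens after randomisation. Comparing raw counts when arms differ in follow-up mixes the episode rate with time at risk.

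**Working it through.** **Step 1: is a change computable?** Baseline instruments described: CFD index, SF-36, PSS-10, IPAQ-SF. WURSS-21 is first supplied at the end of that visit, for use when symptoms occur. Change = follow-up value minus baseline value, and the second term is not collected as described. The schedule figure is not available, so this rests on the visit text.

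**Step 2: the plan's own figure.** No number is given for WURSS-21. The recruitment target comes from the co-primary biomarkers and reproduces: 19 / (1 − 0.30) = 27.1, rounded up to 28 per arm; 28 × 4 = 112. This point does not touch it.

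**Step 3: fit to repeated measures.** Assume Poisson episodes at rate r per person-year (r is not in the article). The chance of at least one form in a 6-month window is p = 1 − exp(−r/2); in all four windows it is p⁴.

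| r per year | p, one window | p⁴, all four |
|---|---|---|
| 0.5 | 22% | 0.2% |
| 1 | 39% | 2.4% |
| 2 | 63% | 16% |
| 3 | 78% | 36% |

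Unless absent forms are scored, a within-person analysis over time has almost no complete cases at the lower rates.

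**Step 4: how ordinary is a participant with no form?** Over 24 months the expected count is 2 at 1 episode per year and 1 at 0.5 per year. The share with none is exp(−2) = 14% and exp(−1) = 37% under Poisson. Under a negative binomial with assumed dispersion 0.5 it is (1 + 0.5 × 2)⁻² = 25% and (1 + 0.5 × 1)⁻² = 44%. True zeros would be common, and unreported episodes would be hidden among them.

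**Step 5: if severity were compared among reporters only.** Simulation with assumed inputs: four arms, 20 per arm (28 × 0.7 = 19.6, rounded up), 1,500 runs, one arm with half the episode rate and the same severity per episode. Kruskal–Wallis on mean severity among reporters rejects in about 6% of runs. The same test on total burden with zeros included rejects in 63% (1 episode per year in the other arms) and 91% (2 per year).

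**Step 6: if raw counts were compared under unequal dropout.** With exits uniform over 24 months, mean follow-up is (1 − d) × 24 + d × 12 months.

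- Dropout 20% against 40%: 21.6 and 19.2 months, ratio 0.89.
- Dropout 10% against 40%: 22.8 and 19.2 months, ratio 0.84.
- Dropout 30% in both: 20.4 and 20.4 months, ratio 1.00.

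Null simulations with assumed inputs (1.5 episodes per year, dispersion 0.5, 28 per arm, two arms, every early leaver kept) give these Kruskal–Wallis rejection rates: about 8% for 20% against 40%; roughly 11% to 13% across repeat runs for 10% against 40%; and about 5% at equal 30%. A negative binomial model with log follow-up time as offset gave a ratio of 1.00 and rejection of 5.4% and 4.3% in the two unequal cases.

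**Step 7: sensitivity to the analysis set.** Suppose the 80% compliance rule removes anyone followed for less than 0.8 × 24 = 19.2 months (an assumption; the article does not say how it treats early leavers). The ratios then become about 0.99 and 0.98 and rejection about 5%. With four arms at 20/20/20/40% dropout and all leavers kept, rejection is about 7%.

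**The case against.** The strongest reply is that this is a wording slip plus detail that an article leaves to a fuller document. Much of it is fair.

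- **Returned forms only.** A reader might infer that the analysis will use only returned forms. The article does not say so. It ties no test to WURSS-21, gives the nonparametric tests as examples, and names incidence as an aim, which requires counting people without an episode. Kruskal–Wallis on per-participant totals with zeros would be usable.
- **Unequal follow-up.** A reader might also infer that the comparison is biased by dropout. The article gives one dropout figure, 30%, with no difference between arms. Forms are gathered in 6-month windows, so people attending a visit have about equal exposure in that window. The simulated distortion needs a gap of 20 to 30 percentage points and retention of all early leavers. The compliance rule may remove many of them.
- **Importance.** The abstract mentions immunity but does not link it to WURSS-21, and the Discussion stresses the study's explorative character. It would go too far to say that this outcome carries that claim.
- **The word change.** The outcomes sentence could be read so that it covers only the indicators of ageing. The reading that covers all three items is the more natural one.

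What survives is the mismatch between stated passages, and the data-collection gap. No later analysis document can separate an unreported episode from no episode if nobody asked.

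**Conclusion.** The point holds in a limited form. As described, WURSS-21 cannot give the change that the outcomes section most naturally promises. Two sections label it differently, and the generic repeated-measures plan does not fit symptom-triggered forms. These conclusions rest on the text alone, subject to the schedule figure that is not available.

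The numerical consequences are conditional. Loss of the incidence signal (about 6% rejection against 63% to 91%) follows only if reporters alone are compared. Spurious differences (raw-count ratio 0.84 to 0.89) follow only if raw counts are compared with markedly unequal dropout and all leavers kept. Neither analysis is stated, all episode rates are assumed, and at equal 30% dropout the distortion is nil. These figures show what a clear definition would guard against; they do not estimate a bias in this trial.

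This is a cheap and worthwhile improvement to a secondary outcome. It leaves the co-primary outcomes and the target of 112 untouched.

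**What to change.** 1. **Reconcile the text.** Take WURSS-21 out of the outcomes worded as changes, and use one label, secondary or exploratory, in Study outcomes, Table 2 and the instrument section.
2. **Define the measure per participant.** Count episodes from randomisation to last contact, with zero for participants without one. Define total symptom days and summed score the same way, zeros included.
3. **Fit the analysis to it.** Compare episode counts with a count model, for example negative binomial, with arm, gender stratum and log observed time as offset.
4. **Close the collection gap.** At the existing 3-monthly calls and 6-monthly visits, ask every participant whether an episode occurred for which no form was completed. The offset handles time at risk but not unreturned forms; only this question addresses those.

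The cost is revised wording and one question at contacts already planned. The drawback is up to 3 months' recall for unreported episodes. Open-label self-report remains a limitation.
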